## Abstract

**Background:**

Since the *Aedes aegypti* mosquitoes that transmit dengue virus can breed in clean water, WHO-endorsed vector control strategies place sachets of organophosphate pesticide, temephos (Abate), in household water storage containers. These and other pesticide-dependent approaches have failed to curb the spread of dengue and multiple dengue virus serotypes continue to spread throughout tropical and subtropical regions worldwide. A feasibility study in Managua, Nicaragua, generated instruments, intervention protocols, training schedules and impact assessment tools for a cluster randomised controlled trial of community-based approaches to vector control comprising an alternative strategy for dengue prevention and control in Nicaragua and Mexico.

**Methods/Design:**

The Camino Verde (Green Way) is a pragmatic parallel group trial of pesticide-free dengue vector control, adding effectiveness to the standard government dengue control. A random sample from the most recent census in three coastal regions of Guerrero state in Mexico will generate 90 study clusters and the equivalent sampling frame in Managua, Nicaragua will generate 60 clusters, making a total of 150 clusters each of 137–140 households. After a baseline study, computer-driven randomisation will allocate to intervention one half of the sites, stratified by country, evidence of recent dengue virus infection in children aged 3–9 years and, in Nicaragua, level of community organisation. Following a common evidence-based education protocol, each cluster will develop and implement its own collective interventions including house-to-house visits, school-based programmes and inter-community visits. After 18 months, a follow-up study will compare dengue history, serological evidence of recent dengue virus infection (via measurement of anti-dengue virus antibodies in saliva samples) and entomological indices between intervention and control sites.

**Discussion:**

Our hypothesis is that informed community mobilisation adds effectiveness in controlling dengue.

**Trial registration:**

ISRCTN27581154.

## Background

Recognition of dengue as a major health issue is increasing, especially in Asia and Central and South America [1]. In Nicaragua and Mexico, as in most dengue endemic countries, the national pesticide-dependent approaches have failed to curb the spread of this mosquito-borne disease. Several reviews have shown pace-spraying with pesticide to kill adult mosquitoes to be of little value [2]. Multiple serotypes of dengue virus continue to move northward through Latin America.

Failure to curb the dengue epidemic has led to resurgence of interest in community mobilisation for its vector control. A 2007 systematic review of community-based dengue control programmes, including two randomised controlled trials, found only weak evidence “that community-based dengue control programmes alone and in combination with other control activities can enhance the effectiveness of dengue control programmes” [3]. However, none of these earlier studies used clustered designs.

Several cluster trials have since shown an impact on vector densities. A team in Cuba published a trial of community mobilisation in 16 clusters compared with 16 controls, using vector breeding indices as the outcome [4]. In India, community-level provision of water container covers, clean-up campaigns, and dissemination of dengue information through schoolchildren also reduced vector density [5]. In Thailand, community volunteers reduced vector density [6]. No impact could be detected in a comparison of two communities in the Philippines [7].

A 2011 systematic review of 22 studies involving education messages for community-based dengue prevention concluded that these were effective in reducing entomological indices, but none measured dengue occurrence [8]. A recent systematic review of 14 studies of *Bacillus thuringiensis israelensis* found ample evidence that this reduced the number of *Aedes aegypti* breeding forms but only one study provided any evidence of impact on dengue risk; the study reported one dengue case in the intervention area and 15 cases in the control area [9].

The literature suggests that non-pesticide measures *should* prevent dengue, but there is very little direct evidence of this. A pesticide-free alternative has potential health, economic and environmental benefits.

### Feasibility study in Managua 2004–2008

#### Eligible participants

In Managua, Nicaragua, 10 intervention and 20 control sites (132 houses per site, 3,960 households and 3,300 children aged 3–9 years) piloted development of instruments and protocols for a pesticide-free intervention.

#### Willingness of participants to be randomised

There was no allocation concealment or randomisation to intervention and control. The feasibility study focussed on community intervention dynamics and development of impact assessment instruments.

#### Interventions

Baseline survey teams collected serological, entomological and behavioural evidence during biannual measurement cycles. Community volunteers used this evidence to promote dialogue on the issue of dengue prevention and to develop interventions in 10 sites. Interventions included household visits, active demonstration of mosquito eggs and larvae/pupae in the home, and use of simple tools and procedures for breeding site elimination.

#### Follow-up and response rates to questionnaires

Of 5596 households contacted in 2008, all allowed examination of vector reservoirs outside the building; all but 21 answered questions about recent illness in the household (99.7%).

#### The proposed outcome measures

Planned outcomes were serological IgG ELISA analysis of paired saliva samples to detect a decrease in the serological evidence of recent dengue virus infection in children aged 3–9 years; entomological indices; and household measures of social capital. Evaluation teams measured entomological, immunological and behavioural indicators each year. Covariates included use of temephos, type of water container, other containers near the dwelling, education of household head, involvement in other community matters, and number of people in the household.

#### Standard deviation of the outcome measure, to estimate sample size

In 2004–8, incidence of dengue virus infection in children over the two measurements ranged between 1.5% and 7.4% in the control communities; the reporting rate of dengue varied between 0.6% (1/166) and 5.3% (10/189); between 11% (20/183) and 50% (94/188) households were positive for *Aedes aegypti* larvae and/or pupae.

#### Adherence/compliance rates

The total 3,217 households with children aged 3–9 years yielded 2,992 saliva samples from these children (7% or 225 declined or were not present at the time of the visit). By the fourth year of the feasibility study (2007), twice as many households in the intervention sites (15.5%) as in the control sites (7.1%) said they participated directly in community dengue control exercises, and 50.7% in intervention and 39.5% in control sites reported having looked for larvae in their water stores over the last week.

#### Intraclass correlation coefficient (ICC)

Using an ANOVA framework for the 20 control communities in 2007, we estimated an ICC of 0.78 for the saliva samples of 3–9 year-old children and 0.396 for households positive for *Aedes aegypti* larvae and/or pupae.

#### Comment

As with many studies of this type [10], the feasibility study in Nicaragua was not randomised. We therefore did not evaluate the impact on dengue but estimated parameters needed to design the main study. The Nicaraguan study fine-tuned a dengue-specific intervention strategy called “socialising of evidence for participatory action” (SEPA). The study demonstrated feasibility of Camino Verde in vector control, with likely gains for the intervention communities [11–14]. The long history of community mobilisation in Nicaragua raises issues of replicability in other contexts. We therefore included southern Mexico in the main trial.

### Objectives of the Camino Verde trial

The research question is: Among residents of Managua and the State of Guerrero in Mexico, does evidence-based community mobilisation add effectiveness to the usual dengue control strategies to decrease the risk of dengue virus infection using a parallel group cluster RCT?

The Camino Verde hypothesis is that informed community mobilisation adds effectiveness in controlling dengue. The trial is concerned with the real-life effect of the intervention in the coastal region of Guerrero state and in Managua, rather than its effectiveness under ideal conditions [15, 16].

The overall objective is to reduce dengue risk through evidence-based knowledge translation. An explicit objective is to develop a sustainable community-oriented vector control approach that reduces the need for pesticides in water used in or around homes or areas that children frequent, or likely to be used with food or even as drinking water.

Specific objectives are (1) Determine entomological and serological status of the virus-vector-host ecosystem as well as knowledge, attitudes and behaviour underlying community-led interventions; (2) In partnership with intervention communities, translate this knowledge on dengue vector behaviour and immunology into household and community action against dengue; (3) Identify the impact of informed community mobilisation on dengue risk and its added effectiveness regarding other infections, social capital and longer term economic welfare.

## Methods/Design

### Design of the study

This parallel group pragmatic cluster randomised controlled trial will test informed community mobilisation in dengue control, measured by risk of dengue virus infection, occurrence of self-reported dengue cases, and vector density. The baseline will include a household questionnaire, entomological assessment and saliva samples from children aged 3–9 years. After the baseline survey, a sampling statistician not associated with the trial will randomise the 150 sites to intervention or control, stratified by area, entomological indices and serological evidence of recent dengue virus infection in children. Interventions will be based on evidence of *Aedes aegypti* infestation, explanation of the dengue vector life cycle, and information on how to prevent larvae and pupae from becoming adult mosquitoes. Different ways of transmitting this knowledge and acting upon it will be designed and implemented by the participating communities. The intervention will run for at least a full year. A multi-method impact survey will cover all 150 clusters with no in-cluster sampling. This will measure risk of dengue virus infection, disease reports, and entomological indices of the vector *Aedes aegypti*. Figure 1 is a flow-diagram of the trial.

**Fig. 1 Fig1:**
[figure not shown]
Camino Verde participant flow diagram

### The setting

Nicaragua reports around 10,000 cases of dengue each year; all four serotypes circulate, with one serotype dominating in each season [17]. Between 2003 and 2007, registered dengue cases in Mexico increased 10-fold to 48,456. Guerrero now reports a high rate of dengue haemorrhagic fever (35/100,000), second in the country only to Quintana Roo, with all four serotypes well established. The Nicaraguan and Mexican government strategy for control of the *Aedes aegypti* mosquito rests on insertion of a packet of temephos (trade name Abate) in household water containers, known in both countries as “abatización”.

Participants are residents in a random sample of 150 clusters (100–120 households each) from the latest census in each country. In Mexico, a stratified last-stage-random sample generated 90 enumeration areas, 30 representing each of three regions (Costa Grande, Acapulco and Costa Chica regions of Guerrero state). In Nicaragua, 60 enumeration areas represent of the capital city, Managua, where approximately one-fourth of the Nicaraguan population resides.

### Interventions

“Socialising of evidence for participatory action” (SEPA) (http://www.ciet.org/en/method/sepa-communication/), was fine-tuned during the Managua feasibility study. Although there will be a high degree of local customising of the intervention, all sites will follow the same protocol to generate community-wide activities that vary widely in character and scope but all built around information about the life cycle of the mosquito and how to interrupt it:Feedback of evidence from the baseline survey to community representatives in discussion groups to author the locally-defined interventions;
*Brigadistas* or volunteers from the communities will serve as organisers and as educators -- trained by facilitators from the research team, who will then be withdrawn from the communities -- conducting visits to schools and household (*visitas de acompañamiento*) to show the evidence of infestation in water receptacles;Structural interventions will change the Aedes aegypti ecosystem in each intervention community;Intercommunity visits and peer evaluations will share experiences between communities and strengthen the group dynamics and the collective preventive action.

In both intervention and control enumeration areas, interviewers from the baseline survey will return individual serology results and explanations of their interpretation to households where 3–9 year old children provided saliva samples. Other activities will depend on community preferences and, based on the feasibility study and discussions with pilot communities, could include neighbourhood clean-up campaigns, puppet theatre, basketball competitions, rap (reguetón) and other songs about dengue, parades, and poster competitions.

Community-to-community peer monitoring is an anticipated feature of the intervention, to be customised to suit the different conditions in the two countries. In Nicaragua, the four-year feasibility study has already provided a good idea of the change process so their emphasis may be more on the quantitative data. Both Mexican and Nicaraguan peer process evaluations will involve members of the research team from one cluster or region visiting another cluster or region and gathering both quantitative and qualitative information to provide project management and community leaders with actionable details about the intervention process, to inform any necessary mid-course corrections. In both countries, the inter-community visits and process evaluation will provide encouragement and training for intervention field staff and communities alike.

Quantitative information will include data on the last time a member of the cluster’s own research team visited the household and data on larval/pupal infestation as found by the monitoring team. Qualitative information will include recommendations from householders for improvement in the programme and responses to questions about the most significant change that community members have observed since the intervention began [18]. With the focus on the nature of the change, purposive sampling will yield a number of accounts to be processed [19].

### Outcomes

The main outcome measures are (i) risk of dengue virus infection as measured by a minimum of two-fold increase in anti-dengue virus IgG antibodies across paired saliva samples collected before and after the 2012 dengue season in children aged 3–9 years [20] (ii) dengue cases (any age) in the last year reported by the household respondent; and (iii) entomological indices of *Aedes aegypti* breeding sites, using the protocol developed in the Nicaragua feasibility study [21].

#### Serology samples

Interviewers who have not been part of the intervention will collect saliva samples from children (estimating ~140 households in each cluster, one child aged 3–9 years in every three households) in both intervention and control clusters at the beginning and at the end of the dengue season. During household visits, the interviewer will ask children to spit 0.5–2 ml of saliva into a plastic receptacle. Returning fieldworkers will transport samples to the CIET laboratories in Acapulco and the Ministry of Health National Virology Laboratory in Managua, divided into labelled aliquots and stored at −80 °C until processing. We will process the pre- and post-season samples side-by-side by capture ELISA and will consider an increase in IgG antibody units of greater than or equal to two-fold indicative of increased dengue virus infection risk. The analysis will be repeated for three-fold and four-fold changes.

The serology protocol requires incubation of polystyrene plates fixed with 100ul anti-human IgG antibodies (Sigma) incubated for 24 h, then incubated at 37 °C for one hour with 50 μl of undiluted saliva, followed by incubation for 1 h with 50 μl of antigen prepared from all four dengue serotypes prepared in-house in Nicaragua from infected mouse brain, with four washes in between each step. We will measure the colour change after adding 50 μl of anti-dengue virus immunoglobulin conjugated to horseradish peroxidase (prepared and titrated in Nicaragua) followed by 50 μl of TMB substrate (Sigma) at 450 nm in an ELISA reader. We will calculate antibody units as = [(OD sample - OD negative control)/(OD positive control - OD negative control)] × 100.

#### Breeding site assessment

Entomology evaluators who are unaware of the intervention status of sites will inspect indoor and outdoor containers, including natural habitats such as tree holes and leaf axils, that might harbour *Aedes aegypti* or *Aedes albopictus* immature forms (larvae or pupae). They will examine containers in dark or shaded areas using flash lights. Although recent research questions the value of *Aedes aegypti* larvae as a predictor of adult mosquito females in households [22–24], we include larval indices as both Mexican and Nicaraguan Ministries of Health rely on these for dengue mosquito surveillance [25]. Evaluators will examine all container types (tires, flower vases, water storage barrels, laundry wash basins, plastic tarps, puddles, and discarded containers (bottles, cans, drums, metal pots, plastic containers) [26]. They will collect all the larvae and pupae from each positive container using nets and pipettes, place them in labelled and capped plastic vials, and send them to the National Entomology Reference Laboratory in Nicaragua and CIET Entomology Laboratory in Mexico for identification. Double data entry with discrepancy verification will reduce keystroke errors before linking data with other study databases.

#### Entomology indices

These are a) House Index (HI), number of houses with one or more containers positive for immature *Aedes aegypti* divided by the number of houses sampled multiplied by 100; b) Container Index (CI) number of water-holding containers with immature *Aedes aegypti* divided by the number of water-holding containers inspected multiplied by 100; c) Breteau index (BI) number of water-holding containers with immature *Aedes aegypti* per every 100 households inspected; d) pupae per container or household inspected; and e) pupae per person (pu/per) number of pupae collected over the total number of inhabitants of the households inspected.

Secondary outcomes focus on the social capital gained from community engagement and the partial outcomes toward acceptance of the Camino Verde, including knowledge of and attitude to prevention, intention to change prevention behaviour, agency (collective and self-efficacy), discussion/socialisation, and prevention-related action. Additional secondary outcomes include purchase and use of pesticide, and reduced expenditure on health care as a consequence of dengue virus infection.

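### The Container Index, and pupae per container if that version is used, divide by containers the intervention may remove, so as between-arm outcomes they can understate, hide or reverse a real fall in breeding sites

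*Protocol article*

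**What the plan says.** The Outcomes section names three main outcome measures; the last is introduced as "and (iii) entomological indices of" *Aedes aegypti* breeding sites. The Entomology indices section then lists five, unranked:

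- House Index: positive houses "divided by the number of houses sampled multiplied by 100".
- Container Index: positive containers "divided by the number of water-holding containers inspected multiplied by 100".
- Breteau index: positive containers "per every 100 households inspected".
- "d) pupae per container or household inspected", with no choice made between the two denominators.
- Pupae per person: "number of pupae collected over the total number of inhabitants of the households inspected".

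The Principal analysis section treats vector indices as continuous variables in a cluster-level t-test. It reports outcomes by arm with relative risk reductions and 95% confidence intervals. The one entomological variable it spells out is the percentage of positive households in each site.

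On the intervention, the trial's Interventions section says that structural measures will alter the mosquito's ecosystem in every intervention community, and that other activities "could include neighbourhood clean-up campaigns". The feasibility study's intervention included "use of simple tools and procedures for breeding site elimination". The Breeding site assessment section counts tires, tarps and discarded bottles and cans among the containers examined.

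**The concern.** A between-arm comparison of a ratio shows an effect on the numerator only if the intervention leaves the denominator alone. The number of water-holding containers found at follow-up is observed after randomisation, and the intervention may lower it. Clearing away breeding sites then reduces both parts of the Container Index. What remains is positivity among the surviving containers, which differs from the number of breeding sites to which residents are exposed.

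At stake is the reading of a main outcome. The Container Index and the Breteau index have the same numerator, yet could point in different directions for an arithmetic reason alone. A relative risk reduction in the Container Index would not measure reduced vector exposure. No section of the article addresses this.

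**Working it through.** **Inputs.** The index definitions come from the Entomology indices section. The article gives no container counts, container positivity or pupae per positive container, so there is no figure of the plan's own to reproduce on this point. Its sample size calculation concerns serology and does not enter. All counts below are assumptions.

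**Identity.** Over the same inspected houses, let P be positive containers, N water-holding containers and H houses.

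- Container Index = 100 × P/N
- Breteau index = 100 × P/H
- Hence Container Index = Breteau index ÷ (N/H)
- In the same way, pupae per container = pupae per household ÷ containers per household

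The intervention-to-control ratio of the Container Index is thus the Breteau ratio divided by the ratio of containers per house. This is exact within a cluster or for pooled counts, and approximate for means of cluster values. If containers per house fall, the Container Index shows less benefit than the Breteau index. If positive and negative containers fall in equal proportion, it does not move. If negatives fall in greater proportion, it rises.

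**Example 1.** Assume 140 households, 3 containers each (N = 420), 10% positive (P = 42) and 10 pupae per positive container. In every scenario, positive containers fall by 40%, to 25.2.

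| Scenario | N afterwards | Container Index | Breteau index | Pupae per container | Pupae per household |
|---|---|---|---|---|---|
| Before | 420 | 10.0 | 30 | 1.00 | 3.0 |
| 40% of positives cleaned, all kept | 420 | 6.0 | 18 | 0.60 | 1.8 |
| 40% of positives, 20% of negatives removed | 25.2 + 302.4 = 327.6 | 7.7 | 18 | 0.77 | 1.8 |
| 40% of each removed | 25.2 + 226.8 = 252 | 10.0 | 18 | 1.00 | 1.8 |
| 40% of positives, 60% of negatives removed | 25.2 + 151.2 = 176.4 | 14.3 | 18 | 1.43 | 1.8 |

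The Breteau index and pupae per household fall by 40% throughout. The Container Index shows a 40% fall, a 23% fall, no change, or a 43% rise (14.3/10.0). With 5% positive at the start, it goes from 5.0 to 3.0, 3.8, 5.0 and 7.3. With 5 containers per house the Container Index values are the same.

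If only positive containers are removed and all negatives stay, the index is 25.2/(25.2 + 378) = 6.25%. That is a 37.5% fall against 40%, so the distortion is then slight.

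**Example 2, two container types, per 100 houses.** Control: 300 discards at 5% and 200 storage containers at 25% positive.

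- Control: (15 + 50)/500 = 13.0%, Breteau 65.
- Three-quarters of discards removed and storage positivity cut by a quarter: (3.75 + 37.5)/275 = 15.0%, Breteau 41.25. The Breteau index is 37% lower and the Container Index 15% higher.
- Half of discards removed, same cut in storage positivity: (7.5 + 37.5)/350 = 12.9%, Breteau 45. The Breteau index is 31% lower and the Container Index almost unchanged.
- Break-even with three-quarters removed: 3.75 + 50(1 − r) = 0.13 × 275 = 35.75, so r = 0.36. The Container Index falls only if storage positivity drops by more than 36%.

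**The case against.** The strongest reply is that the plan does not lean on the Container Index. The only entomological variable spelled out for the principal analysis is household-based, and ranking the indices is commonly left to an analysis plan, which is not shown. The index is correctly defined. The article also gives its reason for keeping larval indices, namely that both ministries rely on them, while acknowledging doubts about their predictive value. Item d) already offers a household denominator, and its container denominator is not said to be water-holding.

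A second reply is that the listed set exposes the artefact. Breteau divided by Container Index returns containers per house: in Example 2, 65/13.0 = 5.0 against 41.25/15.0 = 2.75.

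A third is that the extent of removal is inferred. The explicit wording on eliminating breeding sites describes the non-randomised feasibility study. In the trial, clean-up depends on community preference, and the structural measures are not specified as removal. Showing families the larvae in their water stores is equally compatible with cleaning containers that stay in use.

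Most of this stands, as a limit on the point. It rules out any claim that the whole entomological outcome is compromised, and it confines the pupal point to the per-container version. It does not remove the point. The article itself fixes the Container Index denominator, places the index under a main outcome on equal terms with the others, and takes vector indices generally into the between-arm analysis. Ministry use is a reason to report the index, but not to test it as an effect of treatment. That a reader could recover the container count by division does not make a relative risk reduction in the Container Index a valid summary.

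**Conclusion.** The point holds in a limited form. The Container Index, and item d) if taken per container, are unsuitable as between-arm measures of an intervention that may remove containers. The identity needs no assumed data and shows that any net removal weakens, cancels or reverses the apparent benefit relative to the same count per household. How large the distortion would be, and whether it would amount to apparent harm, rests entirely on assumed counts. Serology, reported cases, the House Index, the Breteau index, pupae per household and pupae per person do not carry this fault.

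A reader might infer two stronger things that the documents do not support:

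- That the trial should expect its Container Index to show harm. This needs negative containers to be removed in greater proportion than positive ones, and nothing in the article says they will be.
- That the House Index is biased because its definition refers to houses sampled while other indices refer to households inspected. The design section says there is no sampling within clusters, so the words may mean the same. In the feasibility study every household contacted in 2008 allowed examination of reservoirs outside the building. No figure supports a difference in access between arms.

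This is a cheap improvement to make before analysis, and no threat to the trial's main conclusion on infection.

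**What to change.** In the Principal analysis section, state that the between-arm entomological comparison uses measures per house, per household or per person: House Index, Breteau index, pupae per household and pupae per person. In the Entomology indices section, set item d) to pupae per household inspected. Report the Container Index and pupae per container descriptively, beside the mean number of water-holding containers per household in each arm, so that removal is visible directly.

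The cost is wording in those two sections. The container inspections are already planned, so no new data are needed. The small downside is that an index the ministries use is no longer tested as an intervention effect, although it is still reported.
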